## Abstract

**Background:**

Pediatric depression is a global concern that has fueled efforts for enhanced detection and treatment engagement. As one example, the US Preventive Services Task Force recommends depression screening for adolescents ages 12–18 years. While many health systems have implemented components of depression screening protocols, there is limited evidence of effective follow-up for pediatric depression. A key barrier is timely team communication and coordination across clinicians and staff within and across service areas for prompt service linkage. However, team effectiveness interventions have been shown to improve team processes and outcomes and can be applied in healthcare settings.

**Methods:**

This project aims to refine and test a team communication training implementation strategy to improve implementation of an existing pediatric depression screening protocol in a large pediatric healthcare system. The team will be defined as part of the study but is expected to include medical assistants, nurses, physicians, and behavioral health clinicians within and across departments. The implementation strategy will target team mechanisms at the team-level (i.e., intra-organizational alignment and implementation climate) and team member-level (i.e., communication, coordination, psychological safety, and shared cognition). First, the project will use mixed methods to refine the team training strategy to fit the organizational context and workflows. Next, a hybrid type 3 implementation-effectiveness pilot trial will assess the initial effectiveness of the team communication training (implementation strategy) paired with the current universal depression screening protocol (clinical intervention) on implementation outcomes (i.e., feasibility, acceptability, appropriateness, workflow efficiency) and clinical/services outcomes (increased frequency of needed screening and reduced time to service linkage). Finally, the study will assess mechanisms at the team and team member levels that may affect implementation outcomes.

**Discussion:**

Team communication training is hypothesized to lead to improved, efficient, and effective decision-making to increase the compliance with depression screening and timely service linkage. Findings are expected to yield better understanding and examples of how to optimize team communication to improve efficiency and effectiveness in the pediatric depression screening-to-treatment cascade. This should also culminate in improved implementation outcomes including patient engagement critical to address the youth mental health crisis.

**Trial registration:**

NCT06527196.

Trial Sponsor: University of California San Diego.

**Supplementary Information:**

The online version contains supplementary material available at 10.1186/s43058-024-00641-5.

Contributions to the literature
Effective youth depression screening and care linkage is hindered by implementation challenges including communication and coordination gaps across service systems, organizations, and providers.This study will leverage team effectiveness interventions and implementation science by testing a multilevel team communication implementation strategy that targets provider and organizational-level mechanisms to improve the youth depression care cascade.Results of this study are expected to inform implementation strategies to enhance timely and more responsive youth depression screening and treatment, which will in turn improve outcomes for pediatric patients in need of mental health care.

## Background

### Depression screening for pediatric patients

Data from the National Survey of Children’s Health indicates a 3.2% prevalence rate for pediatric depression in the US and 14.3% among youths with serious co-occurring and life-limiting medical conditions [1]. Even more concerning are results from a recent meta-analysis indicating a global 25.2% prevalence rate of pediatric depression during COVID-19 [2]. This, along with the recent US Surgeon General’s Advisory on the youth mental health crises that has been exacerbated by the COVID-19 Pandemic, refocuses the need for effective and efficient screening and treatment for pediatric depression [3, 4]. While many pediatric healthcare systems and clinics are aware of this need, there is little evidence of widespread effective follow-up for pediatric depression [5].

### The clinical intervention: depression screening and referral to treatment

The US Preventive Services Task Force recommends depression screening for adolescents 12–18 years old [6]. Many pediatric healthcare systems are implementing depression screening protocols across medical subspecialities, including Rady Children’s Health Network [7]. The screening to treatment “cascade” includes screening, clinical recognition of a problem, referral, treatment initiation, and treatment response [8]. Successful implementation requires effective and optimized inter-provider communication and coordinated treatment planning to facilitate timely review and health system response for at-risk youth.

The implementation context is Rady Children’s Health Network that currently employs a multi-step early identification universal depression screening protocol (the clinical intervention) embedded within the electronic health record (EHR) in multiple specialty units with an existing behavioral health referral service described in Crandal et al. [7]. In this study, all patients who are 12 years and older are expected to be screened using the Patient Health Questionnaire (PHQ) at every encounter within the Emergency Department, primary care, urgent and acute care, inpatient specialty, or within 30 days of outpatient medical appointments if it has not already occurred. Patients are first administered the PHQ-2 [9]. Those who endorse a PHQ-2 score of 3 or greater are then administered the remaining questions on the PHQ-9 [10]. Patients who endorse a PHQ-9 score of 10–19 indicating moderate-severe depression symptomology, but not elevated risk for suicide, are referred to meet with a behavioral health professional and offered educational materials, as well as additional service referrals. This approach focuses primarily on the recognition/identification component of the depression treatment cascade outlined by Pence et al. in 2012 [8].

### Implementation gaps in depression screening

Effective implementation requires a team of individuals across the cascade to communicate and coordinate in a clear and timely manner. Although system-wide interventions such as universal screening policies and mutual access to EHRs between provider specialties can be facilitative, implementation gaps remain in the depression treatment cascade [11]. For example, not all children are screened, and for those who are screened, timely follow-up and linkage to care in response to elevated scores does not consistently occur. More recent and detailed local data [7] support these implementation gaps. All adolescents screened at risk for moderate-severe depression receive a list of behavioral health self-referral options including internal and external services. However, only internal behavioral health referrals are tracked uniformly at Rady Children’s Health Network.

This project proposes that intra-organizational alignment can serve as a mechanism potentially mediating the association of organizational context (e.g., implementation climate) with implementation outcomes [12–14] (e.g., acceptability, appropriateness) to mitigate gaps in the referral to treatment cascade. This approach is consistent with recent developments in organizational research that consider implementation climate and climate strength, a measure of alignment within groups [15]. However, this study will consider intra-organizational alignment across organizational levels. Integrating team effectiveness approaches with implementation science, such as through coordinated specialty care or collaborative care models, is a promising solution to address gaps related to continuous provider communication and coordinated decision-making about evidence-based depression screening, assessment, and service engagement [16–18].

### Team communication training

Team communication training (TCT) is a strategy with a robust evidence base in healthcare settings that has been shown to improve collaborative decision-making, task completion, and health outcomes [19–21]. This study will refine and test TCT (implementation strategy) to target team mechanisms at the team/organizational-level (intra-organizational alignment and implementation climate) and team member/provider-level (communication, coordination, psychological safety, and shared cognition) that will lead to enhanced implementation of an existing pediatric depression screening protocol (clinical intervention). We selected TCT as the team-based implementation strategy because it teaches team members to clearly, concisely, and meaningfully exchange timely and relevant information (i.e., about interpreting depression scores and determining clinical disposition plans). Figure 1 illustrates how this study applies the Implementation Science and Team Effectiveness in Practice (IN STEP) Children’s Mental Health Research Center’s Team Effectiveness for Implementation model [22].

**Fig. 1 Fig1:**
[figure not shown]
Conceptual model of team effectiveness and implementation science

This study will enhance the current active control implementation strategy (automated workflow, decision support tools, and a multidisciplinary taskforce to monitor depression screening compliance and timelines for contacting families) with TCT to improve team mechanisms at the team-level (intra-organizational alignment, implementation climate) and team member-level (shared mental models about roles within the screening/treatment cascade and psychological safety, communication, and coordination within the team). The TCT implementation strategy will be tested using a 2-arm hybrid type 3 pilot trial. We hypothesize that the TCT implementation strategy will engage team mechanisms, which will in turn increase the implementation outcomes of compliance with depression screening and reduced time to service linkage for youth with identified depression risk.

### Assessing team mechanisms at the team and team member levels

Although the team will be refined during the Aim 1 activities, it is expected that the team composition will include medical assistants, nurses, physicians, and behavioral health clinicians (e.g., social workers) within and across departments. Team interactions during a performance cycle impact the formation and refinement of team mechanisms at the team/organizational-level and team member/provider-levels [23]. For example, cognitive emergent states (also known as shared mental models) are important because they are a primary driver of a team’s ability to coordinate interdependent actions [23]. Shared mental models refer to members having a shared understanding of elements such as event milestones, resources, member roles/competencies that are relevant to achieving a team task including effective depression screening, referral, and treatment engagement [23].

In this study, shared mental models refer to shared understanding of the requirements for depression screening, resources following an elevated screen, and role of different team members in the screening to treatment pathway. Also important are affect-based emergent states that drive motivation, effort, and open information exchange as exemplified by psychological safety [23]. The elements of shared cognition can be cognitive and/or affective and indicate the content of shared mental models that can impact team process and outcomes. Improvement in these mechanisms has the potential to improve workflow efficiency by improving “hand-offs” between screening providers and behavioral health assessment/treatment providers. Such hand-offs are associated with increased receipt of services following referral, fewer no-shows or same-day cancellations, fewer days from referral to follow-up behavioral health appointments [24, 25].

We hypothesize that the TCT will be associated with improved implementation outcomes (feasibility, acceptability, adoption, workflow efficiency) and clinical/services outcomes (increased frequency of needed screening and time to service linkage and time to service linkage) compared to the existing universal depression screening implementation condition.

## Method

This study is part of a National Institute of Mental Health Advanced Laboratories for Accelerating the Reach and Impact of Treatments for Youth and Adults with Mental Illness Center [P50MH126231] that supports projects that test team-based implementation strategies that enhance services for children with mental health and developmental needs across systems (schools, specialty mental health, etc.). The project will use mixed methods to refine the team training strategy to fit the organizational context and workflows (Aim 1). A hybrid type 3 implementation-effectiveness pilot trial will then be used to assess the initial effectiveness of the TCT (implementation strategy) paired with the current universal depression screening protocol (clinical intervention) on implementation outcomes (feasibility, acceptability, appropriateness, workflow efficiency) and clinical/services outcomes (increased frequency of needed screening and reduced time to service linkage) (Aim 2). The study will also assess target engagement of mechanisms at the team and team member levels (Aim 3).

### Study objectives

#### Specific Aim 1

Mixed methods will be used to refine a TCT implementation strategy to improve implementation of an existing health system universal depression screening protocol (clinical intervention). We will incorporate organizational team effectiveness research to address implementation challenges associated with health system-wide depression screening protocols. TCT is an effective strategy to enhance communication and decision-making within teams, including in acute healthcare contexts [19–21, 26].

Five focus groups will be conducted with 25 individuals (5 medical specialty clinic leaders, 10 physician or nursing providers, and 10 medical assistants) to identify team (organizational-level) and team member (provider-level) barriers to implementing the existing depression screening protocol. We will also assess workflow efficiency using clinical ethnography and workflow analysis methods [27] to identify specific “pain points” related to screening frequency and time to service linkage. Following rapid analysis [28] of focus group and workflow assessments [27, 29, 30], we will convene a community service working group of pediatric medical specialty clinic and behavioral health care team members to operationalize the components of TCT and tailor for the purposes of increasing the frequency of depression screening and decrease the time to service linkage.

#### Specific Aim 2

A two-arm hybrid type 3 implementation-effectiveness pilot trial will be used to assess the initial effectiveness of the TCT strategy on implementation of the depression screening protocol. The proposed structure and timeline of the TCT is outlined in Table 1. These proposed training components will be refined and finalized based on learnings from the Aim 1 activities with clinic leaders, clinicians, and medical assistants.

**Table 1 Tab1:** Structure and timeline of team communication training

**Team communication training component**	Month 1				Month 2				Month 3				Month 4				Month 5				Month 6			
	1	2	3	4	5	6	7	8	9	10	11	12	13	14	15	16	17	18	19	20	21	22	23	24
Initial training sessions with didactics and simulation exercises (4 h over 2 sessions)	X		X																					
Team performance feedback about intra-team communication in the EHR provided during regular team meetings (15–20 min)		X		X		X		X		X		X		X		X		X		X		X		X
Booster Coaching Sessions (1 h)								X								X								X

Aim 2 will utilize a cluster randomized design in which four specialty care clinics (10 clinicians per clinic; *n* = 40 clinicians) responsible for reviewing and responding to depression screening (youth ages 12–17 years) will be matched and then randomized to a TCT condition (two clinics) versus an early identification universal depression screening condition (two clinics). Clinics will be matched on team size, makeup of the team members, type of medical care focus and then randomized to conditions. Thus, there will be two sets of two matched clinics that will then be randomized, one to the TCT and the other to early identification universal depression screening condition. In the comparison implementation strategy (early identification universal depression screening), multiple discrete strategies will be used including depression screening training in which providers and staff are provided 1) training in the depression screening tool (PHQ), 2) orientation to the clinical pathway (i.e., screening conducted at every urgent care or emergency department visit and every 30 days for all other medical visits), and 3) expectations for handoff to the next step in the care cascade.

The TCT will last 6 months and is proposed to include the following components that will be refined based on Aim 1 findings and developmental activities: Two initial 2-h didactic sessions on effective communication between team members (information-based methods) and simulation exercises based on mock clinical cases (practice-based methods), biweekly performance feedback about intra-team communication in the EHR (demonstration-based methods) provided during regularly scheduled supervision meetings, and a 1 h booster coaching sessions approximately every 2 months over a 6-month period.

#### Specific Aim 3

Mixed quantitative and qualitative methods will be integrated and used to assess team (intra-organizational alignment, implementation climate) and team member (communication, coordination, psychological safety, shared cognitions) mechanisms of the TCT implementation strategy and a novel application of natural language processing methods. This project will both benefit from and contribute to the IN STEP Methods Core work on Natural Language Processing (NLP). Much of the previous work on team communication relied on hand coding utterances to map them to phases and processes of team cognition [31]. We will explore mechanisms of the TCT implementation strategy through semi-structured interviews and surveys. We will also identify and leverage team communication language data sources that are feasible, naturally occurring, and appropriate for the pediatric health system service context (e.g., transcripts from TCT sessions) to submit to the Methods Core for aggregation across projects using natural language processing methods such as automated utterance coding.

### Setting and context

Participants will be drawn from Rady Children’s Health Network, a comprehensive pediatric healthcare system serving more than 700,000 youth in San Diego County (5th largest county in the U.S.), Imperial, and Riverside Counties [32]. Between 2016 and 2020, 95,613 adolescents were screened using the Rady Children’s Health Network depression screening protocol across outpatient specialty care, the emergency department, inpatient medical units, primary care, and urgent care [7]. Of these, 2.4% screened positive for risk for moderate-severe depression. In the calendar year 2021, 77,425 unique adolescent patients were screened and 9.9% evidenced risk for moderate-severe depression on the PHQ [7].

### Participants

Participants from Aim 1 will be recruited from the outpatient ambulatory departments with the highest rates of depression screening and/or behavioral health referrals based on the most recent patient reports from the EHR. These participants will include clinic leaders who oversee clinical operations including depression screening, clinicians and bedside staff who initiate depression screening such as physicians, nurses, and medical assistants, as well as clinicians who manage triage and referral to behavioral health services including social workers, psychologists, and administrative staff (e.g., patient access representatives).

Participants for Aims 2 and 3 will include 40 clinicians or clinical staff (including physicians, nurses, medical assistants, and mental health providers) drawn from the 4 enrolled specialty care clinics (an average of 10 clinicians per clinic). The specialty care clinic structure comprises all relevant members of the care cascade including a clinician who initiates the depression screening, medical provider who support screening completion, a behavioral health provider who responds to both an elevated depression screen and triages to the patient access representatives who are expected to confirm linkage to a behavioral health provider. Based on data from FY 2023, both inpatient and outpatient specialty services have high rates of depression screening.

Although youth are not participants in this project, the focal pediatric population will be youth ages 12–17 years who have a service encounter in the past year. This age range was selected because it aligns with the age range of the current depression screening protocol at Rady Children’s Health Network [7]. De-identified youth patient data will be abstracted from the EHR to determine movement through the screening-to-treatment cascade and workflow efficiency (i.e., time to complete each step in the cascade and referral quality).

### Measures

Multiple measures will be used to assess the outcomes of TCT for Aims 2 and 3. Please refer to Table 2 for a full list of study constructs, outcomes, and the corresponding measures.

**Table 2 Tab2:** Study Constructs and measures (Aims 2 and 3)

Construct		Purpose	Source	Measure	Timepoint
Implementation outcomes	Acceptability, Appropriateness, Feasibility	Outcome	Provider	-Acceptability of Intervention Measure -Intervention Appropriateness Measure -Feasibility of Intervention Measure; Qualitative Interviews	6 mos
	Workflow Efficiency	Outcome	EHR and Provider	-Time from screening to referral via EHR timestamps (referral processing) -Referral to appropriate service (referral quality)	
Team-Level mechanisms	Implementation Climate	Mechanism	Team	Jacobs et al. Implementation Climate Measure [33]	BL, 3 mos., 6 mos
	Intra-Organizational Alignment	Mechanism	Team	Alignment is assessed by the degree to which team members from different organizational levels (e.g., physician, nurse, medical assistant, social worker) exhibit similarity on Psychological Safety Climate and Implementation Climate measures	
Team member-level mechanisms	Communication and Coordination	Mechanisms	Team	Collaboration and Satisfaction About Care Decisions (CSACD)—Collaboration	
	Shared Cognitions	Mechanism	Team	Shared Mental Model via card sorting task	
	Psych Safety	Mechanism	Team	Edmondson’s Psychological Safety Climate	
	Team Indicators	Exploratory	Team	NLP data sources	Monthly; 6 mos
Clinical/service outcomes	Child demographics	Sample characteristics	EHR	Family Demographics Questionnaire	BL, 3 mos., 6 mos
	Clinical outcomes	Outcome	EHR	-Response to elevated depression score -Time (days) to service linkage from elevated depression score	BL, 3 mos., 6 mos
	*Mental Health **Service Linkage*	*Outcome*	*Caregiver*	*-Report of linkage to any mental health service (internal/Rady and external/outside of Rady) following elevated depression score*	*3 mos., 6 mos*
Setting factors	Medical clinic characteristics		EHR and Provider	-# providers -Average patient volume -Patient case-mix: child race/ethnicity, health insurance (public versus private), age	BL

### Implementation outcomes

#### Acceptability, appropriateness, feasibility of intervention measures

This 12-item instrument will be used to capture perceptions of the acceptability, appropriateness, and feasibility of the TCT strategy [34]. Acceptability refers to the degree to which the intervention (in this case TCT) is appreciated or liked, while appropriateness refers to the intervention’s alignment with the specified setting and stakeholders. Feasibility refers to practicality and the likelihood an intervention can be carried out effectively in its assigned setting. Participants provide a value ranging from 1 (completely disagree) to 5 (completely agree) for each item. An individual subscale for each of the three outcomes (acceptability, appropriateness, and feasibility) can be obtained through averaging response values for each question. Participants will complete this measure at the 6-month timepoint following completion of the Aim 2 trial.

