### Data management

#### Analytic plan

For Aims 2 and 3, we will use multilevel modeling with random intercepts and slopes to test the preliminary effects of TCT on implementation and service outcomes (Aim 2) and mechanisms (Aim 3). Refer to Table 2 for measures of outcomes and mechanisms. Specifically, outcomes include team member-reported acceptability, appropriateness, feasibility and workflow efficiency, and child service outcomes. Potential mechanisms are the proposed mediators of implementation climate, psychological safety climate, communication/coordination, and shared cognitions (see Table 2). Clinic will be included as a covariate (fixed effect). To test the effects of TCT a Group [current implementation vs. TCT] X Time [Baseline, 3, 6 Months] cross-level interaction will be assessed for each outcome. If a statistically significant (*p* < .05) interaction term is evident, simple slopes analyses will be conducted.

Quantitative data and qualitative data will be first analyzed separately. First, quantitative analyses of mechanisms of the TCT implementation strategy will be analyzed using the analytic approach described in Aim 2. To examine the hypothesized mediated effects of implementation strategy condition on implementation and service outcomes, multilevel path analysis will be conducted. Measures of Implementation Climate, Intra-Organizational Alignment, Communication and Coordination, Shared Cognitions, and Psych Safety will be tested as mediators in respective models. The specific mediated effects within these models will be tested using the bias-corrected bootstrap approach [38]. Qualitative interview data will be analyzed using rapid qualitative methods [28] based on a templated summary, deductive approach focused on specified team mechanisms. Specifically, the research team will code transcripts for changes in proposed mechanisms as explanatory factors in implementation and service outcomes. We will then use a mixed-methods analytic approach to synthesize the qualitative and quantitative data collected to examine convergence (i.e., do the two methods confirm or find similar results), complementarity (i.e., do the two methods provide more depth of understanding of research questions), and expansion (i.e., do the two methods provide insights beyond either method alone).

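### Acceptability, appropriateness and feasibility are defined as ratings of TCT, which only two of the four clinics receive, so the planned between-arm test of these three scales has no interpretable control value.

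*Protocol article*

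**What the plan says.** **What is rated.** The measures section on acceptability, appropriateness and feasibility says: "This 12-item instrument will be used to capture perceptions of the acceptability, appropriateness, and feasibility of the TCT strategy". The definition that follows is equally specific: "Acceptability refers to the degree to which the intervention (in this case TCT) is appreciated or liked".

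**Who rates it, and when.** The same section says: "Participants will complete this measure at the 6-month timepoint following completion of the Aim 2 trial". Table 2 also gives 6 months as the only time point. Under Participants: "Participants for Aims 2 and 3 will include 40 clinicians or clinical staff", drawn from all four enrolled clinics.

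**Who receives TCT.** Under Specific Aim 2, the four clinics are "matched and then randomized to a TCT condition (two clinics) versus an early identification universal depression screening condition (two clinics"). For the comparison clinics, "multiple discrete strategies will be used including depression screening training in which providers and staff are provided" training in the PHQ, orientation to the clinical pathway and expectations for handoff. TCT is not among these.

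**What is compared.** The section on assessing team mechanisms states: "We hypothesize that the TCT will be associated with improved implementation outcomes (feasibility, acceptability, adoption, workflow efficiency") and service outcomes, relative to the existing screening condition. The Analytic plan states: "outcomes include team member-reported acceptability, appropriateness, feasibility and workflow efficiency, and child service outcomes". It assigns every outcome a Group by Time interaction over baseline, 3 and 6 months, with clinic as a fixed effect. It also plans multilevel path models for mediated effects of condition on implementation outcomes, a class that in Table 2 includes these three scales.

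**The concern.** A between-arm test needs the same quantity to be defined in both arms. Here the quantity is an opinion of TCT, and half the clinicians will have no experience of TCT. The measures section makes the scales specific to one arm, while the hypothesis and the Analytic plan treat them as outcomes that both arms share.

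The Abstract and the opening of the Method name four implementation outcomes: feasibility, acceptability, appropriateness and workflow efficiency. Three of these depend on this instrument. The Discussion says the Aim 2 data will serve as preliminary data for a later definitive test. An arm difference on these scales could therefore be carried forward as evidence about TCT when it has no clear meaning. A wrong or missing referent in the questionnaire cannot be repaired at analysis.

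**Working it through.** No figure in the plan decides this point. The 80% power statement does not bear on it: power for an arm contrast presupposes that both arms supply a meaningful score. The check is therefore a reading of the sections side by side, plus two short calculations on the planned model.

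**Step 1. Possible readings of who rates what.**

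| Reading | Fits the measures section? | Consequence for the Group test |
|---|---|---|
| All 40 participants rate TCT | Yes, taken literally | Control clinicians score a strategy they never received; the control mean has no interpretation |
| Only TCT clinicians complete the form | Natural, but not stated | No control data; neither the Group test nor mediation by condition can be run |
| Each arm rates its own strategy | No; the section names TCT as the object | A comparison of opinions about two different strategies; possible, but not declared |

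The first two readings leave no usable control value. The third could give one, but it contradicts the text as it stands. The measures section, the hypothesis and the Analytic plan therefore cannot all stand.

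**Step 2. Which scales are affected, and where.** The hypothesis names feasibility and acceptability but not appropriateness (it lists adoption instead). The Analytic plan names all three. So two scales are affected through the hypothesis, and all three through the Group by Time test and the mediation models.

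**Step 3. How many clinicians can rate TCT from experience.** Two clinics × 10 clinicians = 20. With the plan's 15% attrition, 20 × 0.85 = 17. Per clinic this is 10, or 10 × 0.85 = 8.5 on average.

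**Step 4. Would settling the referent alone rescue the planned test?** Suppose every clinician gave one valid score at 6 months.

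- *Group by Time.* The columns are intercept, Group, Time and Group × Time, four in all. With a single time point, Time is constant, so it is a multiple of the intercept, and Group × Time is a multiple of Group. The rank is 2, and the interaction cannot be estimated.
- *Group at 6 months with clinic as a fixed effect.* The columns are intercept, Group and three clinic indicators, five in all. Each clinic lies wholly in one arm, so Group is a sum of clinic indicators (with the intercept). The rank is 4, and Group is aliased with clinic.

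The timing conflict is separate from the referent problem and is not evidence for it. It matters here because it limits what a comparative repair can look like.

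**The case against.** **The comparator is itself an implementation strategy.** The Background calls it an active control, and Specific Aim 2 lists its parts. A reader might infer from this point that an arm comparison in which each clinician rates the assigned strategy would be invalid. The documents do not support that. How acceptable or feasible clinicians find the strategy they were randomised to is a meaningful contrast, provided it is declared and interpreted as such. This objection stands, and the fix allows for it. It does not rescue the present text, which names TCT as the only object.

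**Nowhere is it said outright that control clinicians complete the form.** This is correct. It follows only from the reference to participants, the definition of participants as clinicians from all four clinics, and the Group test on every outcome. A TCT-only form is a natural reading, and a condensed article may leave administration details to the full protocol. But on that reading the Analytic plan assigns a between-arm test to scales with no control data, so the inconsistency remains.

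**The reach is limited.** A reader might infer that the whole Aim 2 implementation hypothesis is untestable. That goes too far. Workflow efficiency, which its own section labels a primary outcome of the Aim 2 trial, does not depend on this referent, and neither do the service outcomes. For a pilot, ratings of TCT by those who received it are also useful in themselves.

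**Conclusion.** The point holds for three scales. As written, acceptability, appropriateness and feasibility have no interpretable control value, yet all three are assigned a between-arm test and enter the mediation models as outcomes of condition. Two of them, feasibility and acceptability, also appear in the between-arm hypothesis. Experience-based ratings of TCT will come from about 20 clinicians in two clinics, or 17 after 15% attrition.

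This rests on two things: the measures section means what it says in naming TCT as the object, and control clinics do not receive TCT. No other section qualifies either. It does not depend on whether control clinicians are handed the form, because the comparison fails in both cases. Independently, collection at 6 months only means that the Group by Time interaction cannot be estimated for these scales.

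**What to change.** **Main change.** Remove the three scales from the between-arm hypothesis, the Group by Time test and the mediation models. Report them descriptively in the TCT arm, by clinic, with confidence intervals. With two clinics, these intervals describe the clinicians in those clinics rather than clinics in general. If a benchmark is wanted, it should be the sponsor's own and set in advance; the document gives none.

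**If a comparison is wanted.** State in the measures section that each arm rates its own assigned implementation strategy, or that both arms rate a shared object, and interpret the difference accordingly. Use a model that fits the collection times: either a 6-month comparison without the Time interaction, or added earlier assessments where the rated object already exists at that point. A 6-month comparison must also drop clinic as a fixed effect, since arm is aliased with it. Arm then has to be judged against variation between clinics, and four clinics in two arms leave 4 − 2 = 2 degrees of freedom for that, so the result would be imprecise.

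**Align the text.** Bring the hypothesis, the measures section and the Analytic plan into agreement before the questionnaire is fielded.

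**Cost.** The main change alters wording only, with no change to design or sample. It gives up any comparative claim on TCT-specific acceptability, appropriateness or feasibility. The comparative option also changes the questionnaire stem and the model, and possibly adds assessments.
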